## Abstract

Background: Chronic spinal cord injury (SCI) significantly accelerates morbidity and mortality, partly due to the increased risk of cardiometabolic diseases (CMD), including neurogenic obesity, dyslipidemia, and impaired glucose metabolism. While exercise and dietary interventions have shown some transient benefits in reducing CMD risk, they often fail to improve clinically relevant disease markers and cardiovascular events. Moreover, SCI also places caregiving demands on their caregivers, who themselves experience health and functional decline. This underscores the need for more substantial interventions that incorporate appropriate physical activity, heart-healthy nutrition, and behavioral support tailored to the SCI population. Objectives: This randomized clinical trial (RCT) protocol will (1) assess the health and functional effects, user acceptance, and satisfaction of a 6-month comprehensive therapeutic lifestyle intervention (TLI) adapted from the National Diabetes Prevention Program (DPP) for individuals with chronic SCI and (2) examine the impact of a complementary caregiver program on the health and function of SCI caregivers and evaluate user acceptance and satisfaction. Caregivers (linked with their partners) will be randomized to ‘behavioral support’ or ‘control condition’. Methods: Dyadic couples comprise individuals with SCI (18–65 years, >1-year post-injury, ASIA Impairment Scale A-C, injury levels C5-L1) and non-disabled SCI caregivers (18–65 years). Both groups undergo lock-step circuit resistance training, a calorie-restricted Mediterranean-style diet, and 16 educational sessions focused on diet/exercise goals, self-monitoring, psychological and social challenges, cognitive behavioral therapy, and motivational interviewing. The outcome measures encompass the cardiometabolic risks, cardiorespiratory fitness, inflammatory stress, multidimensional function, pain, life quality, independence, self-efficacy, program acceptance, and life satisfaction for SCI participants. The caregiver outcomes include multidimensional function, pain, quality of life, independence, and perceived caregiver burden. Discussion/Conclusions: This study evaluates the effects and durability of a structured, multi-modal intervention on health and function. The results and intervention material will be disseminated to professionals and consumers for broader implementation. Trial Registration: ClinicalTrials.gov, ID: NCT02853149 Registered 2 August 2016.

## 1. Introduction

Chronic spinal cord injury (SCI) is associated with increased risk for cardiometabolic disease (CMD), all-cause cardiovascular disease (CVD), and type 2 diabetes mellitus (T2DM) [1,2]. Pervasive risk factors for these diseases are commonly observed after SCI and are associated with a sedentary lifestyle, hypercaloric nutrition relative to daily need [3,4,5,6], a stark loss of lean tissue [7,8,9,10,11], increased adiposity [12,13], and disrupted regulation of glucose and insulin [14,15]. The Consortium for Spinal Cord Medicine Clinical Practice Guideline for Cardiometabolic Disease Identification and Management identified obesity as the most prevalent cardiometabolic component risk [16], affecting 55–95.7% of the SCI population [17,18]. Alarmingly, obesity is known to pose a more substantial health hazard than the other CMD risks [19,20,21].

The current approach for the management of CMD risks after SCI primarily focuses on exercise rehabilitation and, to a lesser extent, nutritional modification. Studies of moderate-to-intense upper-extremity exercise (70–80% of peak capacity) [22,23,24] and circuit resistance training [25] report reduced individual CMD risks after a short-term intervention. However, the overall benefits typically fail to reach clinically relevant levels or test the sustainability of the intervention. A more reasoned view recognizes the need for a more comprehensive lifestyle intervention for the effective management of cardiometabolic risk factors in individuals with SCI. This requires a multidisciplinary approach incorporating population-appropriate physical activity, ‘heart-healthy’ nutrition at caloric levels that maintain stable body mass, behavioral support to sustain user engagement and long-term compliance, and close monitoring of cardiovascular health indicators [26].

Therapeutic lifestyle intervention (TLI)—involving a combination of physical activity, healthy nutrition, stress management techniques, and educational interventions—typically results in improved overall health and well-being. To address these needs, the Diabetes Prevention Program (DPP) was a landmark NIH-sponsored, 27-center randomized clinical trial that tested a lock-step lifestyle intervention program for persons who were at risk of developing T2DM. The DPP was found to be effective for promoting body mass reduction and lessening the conversion rates to frank diabetes [27,28] and was favorably compared against first-line pharmacotherapy for T2DM [29]. Importantly, programmatic modification of the DPP and testing of the long-term follow-up have shown remarkable success in sustaining—or even further improving—the benefits obtained during the initial treatment. The existing evidence similarly suggests an important role for ‘weight-lowering and fitness-promoting nutrition and exercise’ lifestyle interventions to improve the health and function of people aging with disability [30,31]. Previous studies have emphasized the need for weight management in SCI [32,33], and notably, a preliminary case series in which the DPP was refashioned for persons with SCI found that a clinically significant loss of body mass effectively reduced the component risks for CMD and diabetes [26]. In this way, TLI may be a promising approach for CMD management in SCI that merits further research to fully understand its potential benefits, sustainability, and optimal implementation strategies.

The health state of persons with SCI has recently been shown to impact their caregivers, as they both are living and aging with a disability. As current-day adjuvant providers, caregivers are challenged with assisting daily activities and promoting healthy living for individuals aging with SCI, while they may be similarly experiencing functional and health decline accompanying their own aging [34]. In general, the caregivers of individuals who are dependent on wheelchairs face greater physical demands, frequently needing to engage in activities such as lifting, pushing, or rolling an impaired body. Additionally, they often assume caregiving responsibilities at an earlier stage compared to caregivers of individuals with other physical disabilities. Unfortunately, healthcare plans and research efforts tend to primarily focus on the person with the disability, neglecting the inclusion of caregivers. As a result, it is not surprising that caregivers of individuals with spinal cord injuries (SCIs) experience high levels of pain, anxiety, and depression [35]. While there are limited lifestyle intervention programs targeting cardiometabolic health in SCI, there is an even greater scarcity of programs addressing caregiver health. To the best of our knowledge, there is early evidence supporting the benefits to the care-receiver when a caregiver participates in a linked behavioral intervention program [36]. Consequently, the concept of a coordinated intervention between the caregiver and care-receiver, where both partners can mutually benefit from the intervention, presents an intriguing therapeutic paradigm for consideration.

## 2. Objectives

I.Determine the health and functional impact, and user acceptance and satisfaction, of a 6-month comprehensive TLI adapted from the CDC National DPP in people with chronic SCI;II.Determine the impact and user acceptance/satisfaction of a complementary caregiver curriculum (CCC) program on SCI caregiver health and function.III.Determine whether the CCC enhances the health and functional benefits obtained by the SCI dyadic partner enrolled in the TLI program.

## 3. Hypothesis

I.Participants with SCI will have (a) lower body mass, (b) reduced cardiometabolic risks and inflammatory stress, (c) improved cardiorespiratory fitness and strength, (d) improved multidimensional function, pain, quality of life, and self-efficacy, (e) overall program adherence, and (f) greater life satisfaction following TLI;II.Caregivers of persons with SCI will have (a) lower body mass, (b) reduced cardiometabolic risks and inflammatory stress, (c) improved cardiorespiratory fitness and strength, (d) improved multidimensional function, pain, quality of life, and independence, and (e) reduced perceived caregiver burden, following TLI;III.Participants with SCI will have better outcomes on all of their tested hypotheses if their caregiver partner receives the CCC and not the control curriculum.

## 4. Materials and Methods

### 4.1. Trial Design

This is a prospective randomized, controlled, multi-center intervention adopting a within-subjects repeated measures design, examining persons with disability from SCI and their caregivers who will be co-enrolled as dyadic partners. Following eligibility screening, consent, and randomization (of caregivers only), participants will attend two preliminary sessions including wash-in and baseline assessments (serving as ‘own-control’) prior to beginning in one of the two intervention conditions. Two post-intervention assessments will be conducted, one immediately post-TLI (6 months) and one follow-up (12 months). The trial design is summarized below (Figure 1), was approved by the Human Subjects Research Office, Miller School of Medicine, University of Miami (Institutional Review Board No. 20151065, dated 20 July 2016), and is registered as a controlled trial (ClinicalTrials.gov, ID: NCT02853149 on 2 August 2016).

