### 4.4. Randomization

Given the elevated risk of CMD, the reported benefit of intervention studies on mitigating CMD risk [36], including a preliminary report on the TLI [26], and the ethical imperative to provide effective interventions [37], all participants with SCI will undergo a TLI program modeled after the CDC-supported widely adopted National DPP. The intervention program will incorporate population-targeted exercise, nutrition, and behavioral support in the form of a detailed curriculum, all aspects of which have been tested in a federal grant program at the lead center. Following the completion of baseline assessments, caregivers will be randomized to one of two groups using a stratified approach to achieve equal numbers in persons caring for enrolled partners with paraplegia and tetraplegia. Randomization will be performed independently within each stratum by an independent senior researcher using a list generated by the ‘RAND’ function in Microsoft Excel (Microsoft, Miami, FL, USA). Blinding is not achievable in this intervention study, and therefore neither participants nor research staff will be blinded. Participants are randomly sorted based on generated random numbers—a binary response variable, 0 for the control curriculum group and 1 for the CCC group— and their allocation to groups depends solely on their position in the sorted order. This randomization procedure ensures that participants are allocated to the CCC and control groups in an unbiased and unpredictable manner. Randomization of caregivers serves scientific and ethical purposes by allowing for rigorous assessment and ensuring equitable access to the intervention. Caregivers (linked with their partners) randomized to the test condition will undergo a CCC containing information that is similar to that presented to, but independently taught from, their partners. Caregivers randomized to the control condition will learn a time-matched (i.e., attention/time-controlled) curriculum containing generic information on the overall benefits of exercise and nutrition but lacking any specific exercise/nutritional guidelines, self-management strategies, or nutritional/meal composition. This information will be tailored to people without disabilities and include information the caregiver might otherwise find on the internet. All caregivers, irrespective of randomization, will receive SCI-specific material so that they can provide the appropriate support and best care possible in the framework of the TLI.

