
### 4.5. Trial Participants/Sample Size

The target sample size to be recruited is based on change in the primary outcome measure of body mass in the SCI group. Effect size was calculated based on statistical guidelines established by Cohen [38], similar SCI-related body mass reduction interventions [39], and ES in terms of relative risk reduction for the DPP [29]. Given a significant moderate ES of 0.48, for a two-tailed Fisher’s least significant difference test based on the difference between pre- and post-TLI body mass, with an α = 0.05 and power of 1-β ≥ 0.90, we calculated sample size (N) would require N ≥ 24 per group.

We targeted the enrollment of 30 dyadic couples (30 SCI; 30 caregivers = 60) who satisfy the inclusion and exclusion criteria (outlined below). We assumed an attrition of 20%, yielding an analytic sample size of 48. We note that preliminary data specific to this type of multi-modal and comprehensive TLI in SCI are not available for a direct calculation of ES. It is important to note that power analyses are estimates and assumptions about the effect sizes, and other parameters can vary. Additionally, other factors such as variability in participant characteristics, study design, and protocols can influence statistical power. In this study, we maintain alignment with standard statistical practice and fidelity to the DPP primary trial outcome, body mass, measured before and after the clinical intervention and extension phase.

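### Sections 4.1 and 4.4 give opposite orders for randomisation and baseline assessment; in this open trial the 4.1 order would let known allocation influence the baseline values used to compare the caregiver arms.

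*Protocol article*

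**What the plan says.** **Section 4.1 (Trial Design)** sets out the participant's path: "Following eligibility screening, consent, and randomization (of caregivers only), participants will attend two preliminary sessions including wash-in and baseline assessments". The intervention follows. The same section describes the trial as "adopting a within-subjects repeated measures design", with the pre-intervention values serving as each participant's own control.

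**Section 4.4 (Randomization)** gives the reverse order: "Following the completion of baseline assessments, caregivers will be randomized to one of two groups using a stratified approach". It adds: "Blinding is not achievable in this intervention study, and therefore neither participants nor research staff will be blinded".

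**Section 4.3 (Trial Recruitment)** has written consent signed during the first on-site preliminary session.

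**Table 1** puts the pre-intervention measurements at months -2 and 0. All 16 measures for participants with spinal cord injury (SCI) and all 12 caregiver measures are marked at both times.

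**Section 4.5 (Trial Participants/Sample Size)** sizes the trial on body mass in the SCI group, "based on the difference between pre- and post-TLI body mass".

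**The concern.** A baseline value can be used safely in a randomised comparison because allocation cannot have affected it. Here that depends on which section the sites follow. Under 4.1, an allocation that nobody is blinded to exists before the baseline sessions. Dyads could then change their eating or activity, answer questionnaires differently, put a different effort into volitional tests, or leave because they drew the control curriculum, all before month 0.

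Several Table 1 measures are open to this: food logs, peak exercise and strength tests, self-reported pain and function, and the Credibility and Expectancy Questionnaire, which asks what the person expects of the treatment. The dietary record in section 5.1 is kept partly to detect drift in the caregiver control arm, so the plan itself expects behaviour there to move.

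At stake are the only randomised comparisons in the trial: CCC against control in caregivers (Objective II), and the effect of the caregiver's arm on the SCI partner (Objective III).

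**Working it through.** The plan states no figure on this point, so the check sets the sections side by side and then traces the consequence in symbols.

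**Step 1. The possible orders.** I read the two preliminary sessions as the month -2 and month 0 columns of Table 1, and completion of baseline as the end of the month 0 assessments. Figure 1 is not available to confirm either reading.

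| Order | Month -2 values | Month 0 values |
|---|---|---|
| 4.1 as written: randomise, then both sessions | after allocation | after allocation |
| 4.1 combined with 4.3: consent at the first session, then randomise | before or after, not stated | after allocation |
| 4.4 as written: both sessions, then randomise | before allocation | before allocation |

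The first and third rows exclude each other. The second row shows that 4.3 does not rescue 4.1. If randomisation follows consent, and consent is taken at the first session, randomisation cannot precede both sessions; but month 0 is still measured after it.

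**Step 2. Exposure.** With no blinding, an allocation made before month 0 may be known for up to about two months before the intervention starts. Month 0 is the more exposed measurement. Month -2 opens the wash-in, so even under 4.1 there is less time for behaviour to change before it.

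**Step 3. Effect on a between-arm comparison.** Write D_post for the arm difference in means at month 6 or 12, D_base for the arm difference at month 0, and b for the regression slope of the later value on baseline.

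- Change from baseline estimates D_post - D_base.
- Baseline-adjusted analysis estimates D_post - b x D_base.
- Later values alone estimate D_post.

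If baseline precedes randomisation, the expected value of D_base is 0, and all three estimate the same quantity. If baseline follows a known allocation, D_base can have a non-zero expected value d. The first estimate is then off by d and the second by b x d, relative to the effect of allocation. The third is unaffected by baseline timing, although dropout that depends on the arm before month 0 could still distort it.

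**Step 4. Effect on the sized analysis.** The pre/post body-mass comparison in the SCI group uses no arm difference. Section 4.4 gives the lifestyle programme to every SCI participant whatever the caregiver's allocation. With equal arms, shifts d1 (CCC) and d0 (control) in the SCI partners' month 0 mean would move the overall baseline by (d1 + d0)/2. The partner's own treatment does not depend on the draw, so there is less reason for either shift to be large.

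The documents give no value for d, d1 or d0, and I assume none.

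**The case against.** The best defence is that 4.1 is a one-sentence overview written loosely, that 4.4 is the section meant to govern randomisation, and that 4.4 has the safe order. The consent timing in 4.3 also makes the literal 4.1 order unlikely. No section says when an allocation is disclosed, so knowledge of the arm throughout the wash-in is an inference. A comparison of 6- or 12-month values without baseline would not depend on baseline timing at all.

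Much of this stands. It makes 4.4 the likelier intention and makes the bias conditional. It does not remove the conflict: the article states the order twice, differently, and does not say which section prevails. Figure 1 could not make both sentences true.

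Some stronger readings go beyond the documents:

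- **Randomisation without consent.** A reader might infer this from 4.1 and 4.3 together. But 4.1 itself lists consent before randomisation; the conflict is over timing only.
- **Unequal arms from coin-flip allocation.** A reader might compute a chance of imbalance within strata. But 4.4 says of participants that "their allocation to groups depends solely on their position in the sorted order", which normally fixes group sizes, and it gives no stratum sizes.
- **Sorting needs the whole stratum enrolled first.** The text does not establish this; a sorted list can be prepared in advance and filled in sequence.
- **Centre should have been a stratification factor.** With 30 dyads this is a debatable trade-off, not an error.

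**Conclusion.** The contradiction is certain on the text and should be corrected, because it concerns a rule that the article states and not a detail left to a fuller document. The consequence is conditional. If the 4.1 order is followed, month 0 values, and to a lesser degree month -2 values, can be influenced by known allocation or by arm-related dropout. Change-from-baseline and baseline-adjusted CCC-versus-control comparisons can then be biased. If 4.4 is followed, this source of bias is absent.

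It would go too far to say that every comparison in the trial is biased. The single-group body-mass comparison that sizes the trial is much less exposed, and nothing in the documents shows that 4.1 was the order used. The size of any bias cannot be given from the documents. The conclusion assumes that an unblinded allocation may become known once made, and that the preliminary sessions are the month -2 and month 0 visits.

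**What to change.** 1. In section 4.1, take randomisation out of the steps that precede the preliminary sessions and place it after them.
2. Align 4.1, 4.3 and 4.4 (and Figure 1, if it differs) to one order: screening, consent at the first preliminary session, remaining wash-in and baseline assessments, randomisation, intervention.
3. In section 4.4, state that the independent researcher generates or releases a dyad's allocation only after the month 0 assessments of both members are recorded.
4. If dyads have already been enrolled, report which order was used. If it differed between dyads, report how many were allocated before month 0 and how many of those left before month 0, by arm.

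The cost is wording and one procedural check before release. No visit, measurement or participant is added.

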### 4.2. Trial Setting

All human testing will take place at the lead center in the Lois Pope Life Center at the Miami Project to Cure Paralysis at the University of Miami’s Miller School of Medicine, and at a secondary specialty SCI rehabilitation facility at Craig Hospital (Denver, CO, USA). All biochemical analyses will take place at the Diabetes Research Institute, Division of Endocrinology, Diabetes and Metabolism at the University of Miami Miller School of Medicine.

### 4.3. Trial Recruitment

Candidates will be recruited by informal advertising, personnel referrals, and participant databases at both centers. The Miami Project maintains a database of individuals who have participated in past studies and volunteered additional participation. This is a searchable database under the management of the Director of Education. Institutional Review Board (IRB)-approved advertisements will be posted in the SCI/rehabilitation outpatient clinics at both centers. Basic information about the study status, such as active recruiting, closing, etc., will be searchable in the research section of each participating center’s website (http://www.themiamiproject.org/, (accessed on 2 August 2016); https://craighospital.org/programs/research/research-participation-opportunities, (accessed on 2 August 2016); and additional advertisements such as web blurbs and flyers will be distributed via emails and relevant social media accounts by each center. Upon initial contact, the study will be described and those interested in enrolling will be screened to ascertain eligibility. Written consent will be obtained during the initial on-site preliminary session, and participants will be informed that they can withdraw from the study at any time without consequence. Participants will be paid for their participation in this study. The total value of remuneration for participants at Miami will be USD 750, dispersed in four (4) payments: USD 150 after completion of screening and enrollment, USD 150 after 3 months post training, USD 150 after 6 months of training, and a balance of USD 300 after all data collection is completed at 12 months. The total value of remuneration for Craig participants will be USD 550, dispersed in four (4) payments: USD 100 after completion of screening and enrollment, USD 100 after 3 months post training, USD 100 after 6 months of training, and a balance of USD 250 after all data collection is completed at 12 months. This is primarily designed to reimburse travel expenses and thank them for any inconvenience caused. Compensation differences between sites reflect differences in the cost of living and compensation structures in place at each site to incentivize but not coerce participants.

